### Intervention

In experimental phase, patients will undergo a multidisciplinary review (geriatrician, nurse, clinical pharmacist) of pharmacological treatment upon admission, according to a PCP methodology structured in 4 steps (28): (1a) Person-centred evaluation (person insights): person attitudes and preferences regarding treatment; patient reported outcomes (adherence, burden of treatment, willingness to deprescribe and health status self-assessment). (1b) Person-centred evaluation (clinical insights): comprehensive geriatric evaluation, and definition of therapeutic goals set by the health care team, taking into account the patient preferences. (2) Diagnostic-centred evaluation: review of specific health problems and prescribed chronic treatments considering both current clinical guidelines and the abovementioned treatment intensity. (3) Drug-centred evaluation: identification of drugs with a high iatrogenic potential, interactions, duplications, adjustments for renal/hepatic function and pharmaceutical adequacy. (4) Final therapeutic plan and implementation. Figure 2 shows the followed PCP methodology.

**Figure 2 fig2:**
[figure not shown]
Methodology followed in the intervention phase. CGA, comprehensive geriatric assessment; PROMs, patient-reported outcome measures; QoL, quality of life.

### Control

In the control phase, patients will undergo usual care, described as intermediate medication review, that can be considered as the standard of care (29). It is a reconciliation and treatment review by clinical pharmacists upon admission, considering clinical data, without direct contact with the patients.

### Outcomes

The primary outcome of the study is the mean number of medications per patient.

Secondary outcomes are (see also “Participant timeline and data collection”): prevalence of quantitative polypharmacy and hyperpolypharmacy, qualitative polypharmacy, PIMs, anticholinergic burden, number of underprescribed medications that have been started, ADEs and adverse drug withdrawal events (ADWEs), unplanned care utilization, and mortality. Patient-reported outcome measures (PROMs) will also be secondary outcomes for this study. They include adherence, treatment burden, perceived health status and quality of life, health literacy, and attitudes on deprescription (see Table 1). Finally, another secondary outcome will be the identification of barriers and facilitators of the implementation of the purposed methodology, both at the level of the individual person/healthcare professionals (possible cultural aspects, preferences, etc.) as well as from the system point of view (aspects related to intermediate care).

**Table 1 tab1:** Detailed collected variables.

Demographic variables	Multidimensional assessment	Medication assessment	PROMs
Age Sex Education Family support	Frailty, according to the FI-VIG (53) Dependence in activities of daily living, according to the Barthel Index (54) Dependence on medication management Morbidity, according to the age-adjusted Charlson Comorbidity Index (55) Cognitive impairment, according to the Pfeiffer test (54, 56) Delirium, according to the 4 ‘A’s Test (57) Nutritional status, according to the Mini-Nutritional Assessment – short form (58) Risk of pressure injuries, according to the Braden Scale (59) Need for palliative care, according to NECPAL (60)	Prevalence of quantitative polypharmacy and hyperpolypharmacy (number of patients taking ≥5 and ≥10 medications, respectively; long-term medications will be estimated as the sum of every regularly scheduled medication intended to be administered for a period ≥3 months, including medications with “on demand” dosage) Qualitative polypharmacy: classification of the treatments according to treatment objective (preventive – primary or secondary prevention –, curative/etiological, symptomatic) PIMs, according to the EU(7)-PIM list (61) Anticholinergic burden, according to the ACB score (62)	Adherence, according to the ARMS-e scale (63) Treatment burden, according to the Treatment Burden Questionnaire (64) Health status self-assessment, modified from the Spanish National Health Survey (65) Health-related quality of life, according to the EuroQoL-5D (66) Health literacy, according to a set of 18 health-related words, where the patient is asked to associate each word with either a key term or a distractor from a pair Attitudes on deprescription, according to rPATD questionnaire (67)

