### Participant timeline and data collection

Enrolled patients will be evaluated upon admission for the variables detailed in Table 1 (baseline assessment) and undergo medication review (see “Interventions”). Since the planned intervention will be performed upon hospital admission, we expect nearly total retention. In detail, a trained clinical pharmacist and a geriatrician will perform an evaluation on demographic data, a brief multidimensional geriatric assessment, including the evaluation of the frailty, and data on quantitative/qualitative polypharmacy.

For the intervention phase, PROMs will be assessed upon admission through an interview conducted by a trained clinical pharmacist (see Table 1). Figure 3 summarizes the timeline for the intervention phase.

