**Figure 3 fig3:**
[figure not shown]
Timeline of included subjects. ADEs, adverse drug events; ADWEs, adverse drug withdrawal events; PROMs, patient-reported outcome measures.

In both intervention and control phase, ADEs/ADWEs will be identified by research staff based on a retrospective review of medical records from enrolment to index hospital discharge, or 30 days post recruitment, whatever comes first (post-intervention assessment). We will apply systematic trigger tools suggestive of ADEs/ADWEs occurrence (see Table 2). In detail, the final list is derived from the integration of different validated trigger tools that have been previously used in similar populations. The list was reviewed and validated by geriatricians and pharmacists within the research team (30–32).

**Table 2 tab2:** List of possible “alerts” for ADEs/ADWEs.

Type	Alert
Care alerts	Transfusion or use of blood products
	Code / arrest / rapid response team
	Acute dialysis / Acute kidney injury
	X-ray or Doppler studies for embolism or deep vein thrombosis
	Patient fall
	Immobilization
	In-hospital stroke
	Constipation
	Hypotension
	Lethargy
	Rash
	Unspecified adverse event
	Symptomatic bradycardia
	Delirium
Antidots and treatments	Vitamin K administration
	Antihistamines use
	Flumazenil use
	Naloxone use
	Antiemetic administration (for acute dyspepsia / nausea / vomiting)
	Haloperidol use
	Abrupt medication stop
Medication levels	Digoxin levels >2 ng/mL
	Carbamazepine levels >13 mcg/ml
Laboratory tests	Clostridioides difficile – positive stool
	Serum glucose <50 mg/dL
	Serum glucose >110 mg/dL
	INR > 5
	Haemoglobin or haematocrit decrease >25% / Acute bleeding
	Rising blood urea nitrogen or serum creatinine >2 times baseline
	Estimated glomerular filtration rate <35 mL/min/1.73 m2
	K > 6.0 mEq/L
	K < 2.9 mEq/L
	Na < 130 mEq/L
	ALT >80 U/L and/or AST > 84 U/L
	ALP > 350 U/L and/or total bilirubin >4 mg/dL
	CPK > 269 U/L
	TSH < 0.34 μUI/L or fT4 > 12 μg/dL
	White blood cells <3,000/μl
Emergency department	Emergency department visit within 48 h
	Time in emergency department >6 h
	Readmission within 30 days

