In detail, we will evaluate alert diagnoses: unexpected clinical manifestations occurring during the admission and that might be related or unrelated to the use (or lack of use) of a certain medication. We will also evaluate previously defined altered laboratory tests, according to reference laboratory and literature review. Finally, we will evaluate alert drugs: medications known to be used to correct an alteration produced by a first medication (e.g., naloxone to reverse opioid overdose). All triggers will be further reviewed to discern if they are clearly independent from clinical manifestations related to the patients’ condition. Causality will be then assessed using the 10-point Naranjo Scale (33). The severity of the event will be classified using a modified Hartwig and Siegel scale (34), ranging from trivial (event does not require additional treatment and as no sequalae) to fatal. Avoidability of the event will be assessed using a modified Schumock and Thornton questionnaire (35). Each potential ADE/ADWE form will be evaluated by the blinded members of the ADE/ADWE Adjudication Committee, consisting of a geriatrician and a clinical pharmacist not directly involved in the retrospective review process. In the case of disagreement, additional review by another blinded geriatrician/clinical pharmacist pair of evaluators will be requested. Also, 90 days post-discharge (post-discharge assessment), both experimental and control phase participants will be re-evaluated for quantitative polypharmacy, PROMs, unplanned health care utilization (acute hospital admission, emergency claims), and mortality.

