### Data analysis

Baseline variables will be described using means and standard deviations for quantitative variables and absolute and relative frequencies for categorical variables, with their corresponding 95% confidence intervals. The Student’s t-test will be used to compare means of medications and other qualitative variables, and the chi-squared test will be used to compare polypharmacy, hyperpolypharmacy, ADEs, ADWEs, and other categorical variables. All analyses will be stratified according to frailty and to age groups, as appropriate.

We will perform a generalized lineal model with mixed effects for (individual) time and cluster. In the descriptive analysis we also will perform descriptions for each cluster. The ICC for within-cluster correlation will be analyzed and recalculated with the data result and included in a sensitivity analysis.

Multivariable analyses will be carried out to assess the association between decrease in the number of medications at discharge and possible determinants. PROMs will be assessed by comparison of scores before and after the intervention by using paired t-test for continuous variables and McNemar’s test for categorical variables. Cox proportional hazard models will be used to evaluate the association between intervention and survival or time to first unplanned health care utilization. Missing data will be handled according to multivariate imputations by chained equations. Interim analyses are not planned.

All the analysis of secondary outcomes will only be exploratory as far as the sample size is not powered to detect differences on these variables.

All analyses will be carried out according to the intention-to-treat principle, with statistical significance at *p* < 0.05. STATA and R-Studio software will be used in their most recent versions available for statistical analysis.

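### The primary medication count has no stated time point: the analysis points to discharge, where the visible text schedules no count, and the only scheduled re-count is 90 days after discharge

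*Protocol article*

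**What the plan says.** All references are to the protocol article.

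- **Outcomes:** "The primary outcome of the study is the mean number of medications per patient". No time is attached. The secondary outcomes include "qualitative polypharmacy, PIMs, anticholinergic burden, number of underprescribed medications that have been started".
- **Participant timeline and data collection, admission:** "Enrolled patients will be evaluated upon admission for the variables detailed in Table 1 (baseline assessment) and undergo medication review". Table 1 holds the medication assessment, including the counting rule (long-term medications meant for at least 3 months, on-demand ones included) and "PIMs, according to the EU(7)-PIM list (61) Anticholinergic burden, according to the ACB score (62".
- **Same section, during the stay:** adverse drug events and adverse drug withdrawal events (ADEs/ADWEs) are sought by record review "from enrolment to index hospital discharge, or 30 days post recruitment, whatever comes first (post-intervention assessment"). Nothing else is listed for this assessment.
- **Same section, 90 days after discharge:** "both experimental and control phase participants will be re-evaluated for quantitative polypharmacy, PROMs, unplanned health care utilization", followed by mortality.
- **Same section, retention:** "Since the planned intervention will be performed upon hospital admission, we expect nearly total retention".
- **Data analysis:** multivariable models will "assess the association between decrease in the number of medications at discharge and possible determinants". The sentences on the t-test and the mixed model name no time.
- **Sample size and recruitment:** baseline mean 8.81, expected decrease 1.31, ICC 0.2, 5 clusters, 10 patients per cluster and period, 300 patients, 75% power. No SD and no time point for the decrease are given.

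**The concern.** A count at discharge and a count 90 days later answer different questions. The first measures what the ward team changed. The second measures how much of that change lasted once other prescribers took over, in patients who are still alive and can be reached. A ward effect could be present at discharge and gone at 90 days.

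The trial is open-label and the research team sees the prescriptions. If the time point is not fixed, it can be chosen, even in good faith, once the results are visible. The choice also decides which patients contribute, which effect size the 1.31 should represent, and whether an allowance for loss is needed.

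The appropriateness measures raise a similar but smaller question. Improving the adequacy of treatment is the stated objective, and three of the measures closest to it have no visible date for re-measurement.

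**Working it through.** **1. Schedule against analysis (visible text)**

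| Item | Admission | Discharge or day 30 | 90 days after discharge |
|---|---|---|---|
| Medication count | yes (Table 1) | not listed | yes, as quantitative polypharmacy |
| PIMs, anticholinergic burden, qualitative polypharmacy | yes (Table 1) | not listed | not listed |
| ADEs/ADWEs | – | yes | not listed |
| Decrease in medications used in an analysis | – | yes (Data analysis) | not named |

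The analysis needs a discharge count that the text does not schedule, and the re-count that is scheduled is nowhere called primary. Quantitative polypharmacy is defined in Table 1 from a medication count, so it is fair to read the 90-day item as a re-count.

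**2. Retention**

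The retention statement rests on the intervention being delivered at admission. That is reasonable for a count at discharge. With the average stay of about 30 days given under Study setting, a 90-day post-discharge count falls about 30 + 90 = 120 days after admission. Delivery at admission says nothing about follow-up over that interval, and mortality and unplanned admissions within it are themselves outcomes.

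**3. What loss would cost if 90 days were primary (illustration)**

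Inputs from the document: I = 5 clusters, T = 6 periods (baseline plus five), n = 10 per cell, effect 1.31, ICC 0.2, alpha 0.05. Assumptions: two-sided test, Hussey-Hughes variance for a cross-sectional stepped wedge, one cluster crossing per step.

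Sample size: 5 × 6 × 10 = 300, as stated.

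Design constants, with U the number of treated cells, W the sum of squared treated cells per period and V the same per cluster:
- U = 5+4+3+2+1 = 15
- W = 0+1+4+9+16+25 = 55
- V = 25+16+9+4+1 = 55
- IU − W = 75 − 55 = 20
- U² + ITU − TW − IV = 225 + 450 − 330 − 275 = 70

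Variance of the effect, with τ² = ICC × SD² and s² = (1 − ICC) × SD²/n:

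Var = I s²(s² + Tτ²) / (20 s² + 70 τ²)

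The 75% cannot be checked without an SD, so the SD is solved from it: about 2.745. Then τ² = 1.507 and s² = 0.603. Var = 5 × 0.603 × 9.643 / (12.05 + 105.47) = 0.247, SE = 0.497, and power = Φ(1.31/0.497 − 1.96) = 75%.

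The same SD with fewer analysed patients per cell:

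| Assumed loss | n per cell | Power |
|---|---|---|
| 0% | 10 | 75.0% |
| 10% | 9 | 70.7% |
| 15% | 8.5 | 68.3% |
| 20% | 8 | 65.8% |

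The loss rates are assumptions; the document gives none. Lost patients are treated as contributing nothing. The planned multiple imputation might recover a little from the admission count. Reading the SD as within-cluster changes the solved value to about 2.46 but not the powers in the table.

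**The case against.** The strongest reply is that this is a condensed article whose text already leans towards discharge. Data analysis speaks of the decrease at discharge, and the 90-day contact is described as a follow-up. On that reading the retention statement is sound and the power illustration does not arise. Much of this stands, and it is why discharge is the natural choice. It does not close the gap. The discharge phrase belongs to a secondary analysis of determinants, the primary analysis names no time, and the visible text schedules no discharge count. A time point is part of what the primary outcome is, and the mismatch lies within the document shown.

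Some stronger readings are tempting but not supported:

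- A reader might infer that three time points compete. Admission is labelled baseline, so only two are in play.
- A reader might infer a conflict between an outcome stated as a level and an effect stated as a decrease. In a comparison of control with intervention patients, a lower mean level is the decrease (8.81 − 1.31 = 7.50), so there is no error.
- A reader might infer that appropriateness is never measured after the intervention. Underprescribed medications that were started, and ADEs/ADWEs with their avoidability, are post-intervention measures. The gap is confined to three secondary outcomes, which the plan calls exploratory.
- A reader might take the Figure 3 caption as proof that no discharge count exists. The figure is not shown, and a medication count needs no abbreviation in a caption. The statement must stay with the visible text.
- A reader might attach an inflated type I error to testing both time points. The document plans no such pair of tests, and counts in the same patients would be correlated.

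**Conclusion.** The point holds for the primary outcome. Its time is not stated, the text implies two, and schedule and analysis do not match. Because the trial is open-label and this is the primary endpoint, it should be settled before any outcome data are examined.

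The effect on the result cannot be given as a single figure. If discharge is primary, the retention statement stands and the remedy is mainly one of wording and scheduling. If 90 days is primary, the plan has no stated allowance for loss, and power would fall from 75% to about 71% at 10% loss and about 66% at 20%. Those figures rest on a back-solved SD, a two-sided test and assumed loss rates.

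The missing re-measurement of PIMs, anticholinergic burden and qualitative polypharmacy is a lesser point, subject to what Figure 3 shows.

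**What to change.** 1. In Outcomes, name one primary time point. Discharge fits the determinants analysis and the retention statement best. What matters most is that one is fixed.
2. State that the count follows the Table 1 rule for long-term medications, and schedule it at that time point in both phases.
3. Adjust the mixed model for the admission count, which is already collected.
4. Label the other time point secondary.
5. Align the effect size in Sample size and recruitment, the retention statement, the 90-day list and Data analysis with the choice. If 90 days is chosen, state an allowance for loss and how deaths before the count are handled.
6. Score the EU(7)-PIM list, the ACB score and the treatment-objective class on the same post-intervention medication list in both phases.

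The cost is a revision of wording and schedule, plus a little extra data abstraction and scoring per patient. No additional patients are needed if discharge is chosen.

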### Sample size and recruitment

Sample size was calculated using the Stata command stepped-wedge, considering 5 clusters, a size of each cluster *N* = 10 and five times of measurement after baseline, incorporating one cluster to the intervention phase at each time. Based on previous studies (21), taking a baseline mean drugs of 8.81 and expected decrease of 1.31, we considered an ICC = 0.2 (intraclass correlation). With this data, a sample size of 300 subjects will provide a power of 75%. The sample size was calculated by a statistician within the research group.

For the qualitative part, we aim to recruit and interview 15 older patients with different frailty profiles (mild, moderate, and severe frailty), from both genders. Caregivers of those patients, especially the most severely frail, and 5 geriatricians will also be invited to join the study. We estimate a total of 20–30 participants in this group. Additionally, we aim to include a minimum of 4 focal participation groups (between 5 and 10 people per group), including both patients and healthcare professionals (geriatricians, pharmacists and nurses). The selection of the group participants will be performed to obtain a balanced representation of the different profiles.

### Participant timeline and data collection

Enrolled patients will be evaluated upon admission for the variables detailed in Table 1 (baseline assessment) and undergo medication review (see “Interventions”). Since the planned intervention will be performed upon hospital admission, we expect nearly total retention. In detail, a trained clinical pharmacist and a geriatrician will perform an evaluation on demographic data, a brief multidimensional geriatric assessment, including the evaluation of the frailty, and data on quantitative/qualitative polypharmacy.

For the intervention phase, PROMs will be assessed upon admission through an interview conducted by a trained clinical pharmacist (see Table 1). Figure 3 summarizes the timeline for the intervention phase.

**Figure 3 fig3:**
[figure not shown]
Timeline of included subjects. ADEs, adverse drug events; ADWEs, adverse drug withdrawal events; PROMs, patient-reported outcome measures.

In both intervention and control phase, ADEs/ADWEs will be identified by research staff based on a retrospective review of medical records from enrolment to index hospital discharge, or 30 days post recruitment, whatever comes first (post-intervention assessment). We will apply systematic trigger tools suggestive of ADEs/ADWEs occurrence (see Table 2). In detail, the final list is derived from the integration of different validated trigger tools that have been previously used in similar populations. The list was reviewed and validated by geriatricians and pharmacists within the research team (30–32).

**Table 2 tab2:** List of possible “alerts” for ADEs/ADWEs.

Type	Alert
Care alerts	Transfusion or use of blood products
	Code / arrest / rapid response team
	Acute dialysis / Acute kidney injury
	X-ray or Doppler studies for embolism or deep vein thrombosis
	Patient fall
	Immobilization
	In-hospital stroke
	Constipation
	Hypotension
	Lethargy
	Rash
	Unspecified adverse event
	Symptomatic bradycardia
	Delirium
Antidots and treatments	Vitamin K administration
	Antihistamines use
	Flumazenil use
	Naloxone use
	Antiemetic administration (for acute dyspepsia / nausea / vomiting)
	Haloperidol use
	Abrupt medication stop
Medication levels	Digoxin levels >2 ng/mL
	Carbamazepine levels >13 mcg/ml
Laboratory tests	Clostridioides difficile – positive stool
	Serum glucose <50 mg/dL
	Serum glucose >110 mg/dL
	INR > 5
	Haemoglobin or haematocrit decrease >25% / Acute bleeding
	Rising blood urea nitrogen or serum creatinine >2 times baseline
	Estimated glomerular filtration rate <35 mL/min/1.73 m2
	K > 6.0 mEq/L
	K < 2.9 mEq/L
	Na < 130 mEq/L
	ALT >80 U/L and/or AST > 84 U/L
	ALP > 350 U/L and/or total bilirubin >4 mg/dL
	CPK > 269 U/L
	TSH < 0.34 μUI/L or fT4 > 12 μg/dL
	White blood cells <3,000/μl
Emergency department	Emergency department visit within 48 h
	Time in emergency department >6 h
	Readmission within 30 days

In detail, we will evaluate alert diagnoses: unexpected clinical manifestations occurring during the admission and that might be related or unrelated to the use (or lack of use) of a certain medication. We will also evaluate previously defined altered laboratory tests, according to reference laboratory and literature review. Finally, we will evaluate alert drugs: medications known to be used to correct an alteration produced by a first medication (e.g., naloxone to reverse opioid overdose). All triggers will be further reviewed to discern if they are clearly independent from clinical manifestations related to the patients’ condition. Causality will be then assessed using the 10-point Naranjo Scale (33). The severity of the event will be classified using a modified Hartwig and Siegel scale (34), ranging from trivial (event does not require additional treatment and as no sequalae) to fatal. Avoidability of the event will be assessed using a modified Schumock and Thornton questionnaire (35). Each potential ADE/ADWE form will be evaluated by the blinded members of the ADE/ADWE Adjudication Committee, consisting of a geriatrician and a clinical pharmacist not directly involved in the retrospective review process. In the case of disagreement, additional review by another blinded geriatrician/clinical pharmacist pair of evaluators will be requested. Also, 90 days post-discharge (post-discharge assessment), both experimental and control phase participants will be re-evaluated for quantitative polypharmacy, PROMs, unplanned health care utilization (acute hospital admission, emergency claims), and mortality.

As for the qualitative part, semi-structured interviews will take place during index admission (for patients) and at the end of the study (for professionals). Interviews and focus groups will follow a topic guide and will be audio-recorded. Topic guide will focus on polypharmacy/treatment burden and interventions to improve drug adequacy. In detail, interviews and focus groups will follow a semi-structured guide and will be audio-recorded. We will explore participants’ experiences with polypharmacy and medication review, perceived barriers and facilitators to the implementation of the intervention, acceptability of the PCP approach, and suggestions for improving its integration into routine clinical practice. Recordings will be transcribed and analyzed using thematic analysis (36, 37). Two researchers will independently identify and refine themes through iterative discussion until consensus is reached. The qualitative findings will be used to contextualize and complement the quantitative findings, particularly with regard to implementation outcomes.

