### Study setting

The study will be developed in an urban ICH “Parc Sanitari Pere Virgili,” Barcelona, Spain. The facility includes 360 inpatient beds, divided into geriatric rehabilitation, subacute care, palliative care, and long-term care, and approximately 40 hospital-at-home beds.

Patients will be included from the five geriatric rehabilitation wards. Most of the admitted patients usually come from a hip fracture or a stroke, or they are admitted following a stay in an acute care ward. The medical staff consists of geriatricians and general practitioners, and multidisciplinary team includes nurses, pharmacists, physiotherapists, occupational therapists, psychologists and social workers, among others. The average length of stay per patient is around 30 days.

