
We also acknowledge certain limitations and risks. First, the 90-day follow-up after discharge may vary among the patients, as some may stay at the ICH for longer or shorter periods, influencing the likelihood of following the appropriate therapeutic regimen. Also, we will not conduct specific interventions addressing the various geriatric domains (e.g., cognitive, affective, functional, nutritional), which would vary case by case and could likewise potentially confound the primary and secondary outcomes of the study, also considering the broad inclusion criteria. Moreover, as a monocentric study and the use of a reduced number of clusters, the reproducibility of our findings may be limited. The inclusion of additional centers could have strengthened the potential validity of the evidence deriving from the study. Additionally, given the multidisciplinary nature of the intervention, the applicability and reproducibility of the results in hospitals that are not specifically organized to provide comprehensive assessment and care of older people cannot be assumed and may be limited.

While our hospital maintains stable teams for each ward, we recognize that certain situations could lead to a risk of contamination. If the research team identifies a significant risk in this regard, recruitment may be withhold until the situation stabilizes.

Finally, regarding the sample size, statistical power was set to 75% for the primary outcome in order to guarantee viability of the project and we used previous data from a single center study. Thus, the results will have to be interpreted taking into consideration a possible overestimation of the effect.

Nonetheless, we also acknowledge several strengths. First, its mixed-model design, which is quite original in the literature. Additionally, the use of clusters may facilitate the implementation of the model. Furthermore, considering medications from both qualitative and quantitative perspectives, along with potential ADE/ADWEs, is crucial to enhancing the scientific value of the study, and providing more information on the model’s efficacy and safety.

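### The ADE/ADWE review window does not fit its own readmission trigger, and it gives patients unequal observation time that the chi-squared comparison ignores

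*Protocol article*

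**What the plan says.** All references are to the protocol article.

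- **Window.** Under Participant timeline and data collection, research staff review records in both phases "from enrolment to index hospital discharge, or 30 days post recruitment, whatever comes first". Alert diagnoses are described there as "unexpected clinical manifestations occurring during the admission".
- **Triggers.** The emergency department block of Table 2 lists "Readmission within 30 days" and "Emergency department visit within 48 h". No reference event is given for either.
- **Later follow-up.** In the same section, "90 days post-discharge (post-discharge assessment), both experimental and control phase participants will be re-evaluated". The items are quantitative polypharmacy, PROMs, unplanned care and mortality, with no ADE or ADWE item. Forms go to a blinded adjudication committee, but the text does not say that later admissions generate a form.
- **Stay.** Study setting: "The average length of stay per patient is around 30 days". No standard deviation is given. Only anticipated stays under 72 h are excluded.
- **Analysis.** Data analysis names the chi-squared test for ADEs and ADWEs. It also announces a mixed model for time and cluster, without saying to which outcomes it applies. Observation time is not mentioned for ADEs or ADWEs. Secondary outcomes are declared exploratory.
- **Stated limitation.** Discussion: "the 90-day follow-up after discharge may vary among the patients", because stays differ in length. Nothing similar is said of the ADE/ADWE window.

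**The concern.** There are two separate problems.

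First, the window and the trigger list do not fit together. A readmission follows a discharge, and review ends at discharge or earlier. Staff who follow both rules either never record this trigger, or record it by stepping outside the window for some patients and not others.

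Second, the window is the shorter of the stay and 30 days. A patient discharged on day 10 has a third of the observation of one who stays to day 30, but each counts as one unit in a chi-squared test. The rule is the same in both phases, so this alone creates no bias. In a stepped wedge, however, the control condition sits early and the intervention late. A drift in length of stay over the study, or an effect of the intervention on stay, would change the recorded proportion of patients with an event even if daily risk were constant. Safety, including ADEs, is among the stated objectives, so the comparison will be read.

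**Working it through.** **Plan's own figures.** The article gives no expected ADE or ADWE frequency, so there is none to reproduce. Its sample size follows from 5 wards × 6 periods × 10 patients = 300. One ward crosses over per step, so each condition has 5 + 4 + 3 + 2 + 1 = 15 cells, or 150 patients.

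**Trigger against window.**
- Let discharge fall on day L after enrolment. Review covers day 0 to min(L, 30).
- A readmission after the index discharge falls after day L, and L ≥ min(L, 30). It is outside the window for every L.
- For L above 30, review ends while the patient is still in hospital.

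**Unequal observation.** Inputs:
- From the article: mean stay about 30 days; minimum anticipated stay 72 h (3 days); window capped at 30 days.
- Assumed: enrolment at admission; L = 3 days + a gamma variable, overall mean 30; coefficient of variation (CV) of stay 0.3, 0.5 or 0.75; constant hazard λ of 0.01 or 0.02 events per patient-day.

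Observed time is E = min(L, 30). Over 1,000,000 simulated stays per setting:

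| CV of stay | Discharged before day 30 | Mean E (days) | Share of 30 days unobserved |
|---|---|---|---|
| 0.3 | 54% | 26.4 | 1 − 26.4/30 = 12% |
| 0.5 | 57% | 24.2 | 1 − 24.2/30 = 19% |
| 0.75 | 61% | 21.5 | 1 − 21.5/30 = 28% |

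**Effect on one patient.** The chance of a recorded event is 1 − exp(−λE).
- λ = 0.01: 1 − exp(−0.10) = 9.5% for 10 days; 1 − exp(−0.30) = 25.9% for 30 days.
- λ = 0.02: 1 − exp(−0.20) = 18.1% for 10 days; 1 − exp(−0.60) = 45.1% for 30 days.

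**Effect on a comparison.** Let mean stay be 25 or 35 days in one condition instead of 30, by multiplying the part of the stay beyond 3 days by 22/27 or 32/27. The hazard is unchanged. Recorded percentage with an event, with the change in points from the 30-day column taken before rounding:

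| CV | λ | Mean 30 | Mean 25 | Mean 35 |
|---|---|---|---|---|
| 0.3 | 0.01 | 23.2 | 21.0 (−2.1) | 24.4 (+1.2) |
| 0.3 | 0.02 | 40.8 | 37.5 (−3.3) | 42.8 (+1.9) |
| 0.5 | 0.01 | 21.3 | 19.5 (−1.7) | 22.5 (+1.2) |
| 0.5 | 0.02 | 37.7 | 34.9 (−2.8) | 39.7 (+1.9) |
| 0.75 | 0.01 | 19.0 | 17.6 (−1.4) | 20.1 (+1.1) |
| 0.75 | 0.02 | 33.9 | 31.6 (−2.3) | 35.7 (+1.7) |

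The spurious difference is 1.1 to 3.3 points.

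**Scale.** With 150 patients per condition and 21.3% with an event, the simple standard error of a difference is √(2 × 0.213 × 0.787 / 150) = 4.7 points, ignoring clustering and period. The shift is smaller than one standard error.

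**The case against.** The strongest reply is that the rule is identical in both phases, the outcome is secondary and declared exploratory, and nothing in the article suggests that stay will differ by condition. All of that is true. It limits the bias to the case where stay differs by condition or period, and keeps it to a few points. It does not mend the mismatch between trigger and window, which depends on no such difference.

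It can also be said that Table 2 gives the readmission trigger no reference event. The list is merged from existing tools, and this is one entry among about 40. The index stay might itself be meant as the readmission, but nothing says so, and the post-discharge reading is the natural one. Readmissions are not lost as data, since acute admissions and emergency claims are collected at 90 days; what is missing is the route to adjudication. Figure 3, the timeline, is not available here and might bear on this.

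A reader might infer four stronger points that the article does not support:

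- **That the survival analyses start at discharge and so leave out in-hospital deaths.** Data analysis gives no time origin for the Cox models. The 90 days after discharge is an assessment date, and the origin is a detail that an article may leave to the full plan.
- **That the distortion is about 8 points.** At λ = 0.01, a 20-day window gives 18.1% and a 30-day window 25.9%. That compares two window lengths, not two trial conditions.
- **That missed late withdrawal events materially favour the intervention.** The review takes place on admission, so for a stay near the average most of the following month is inside the window. Some later events will be missed, especially after short stays, but the article gives no basis for a size.
- **That detection always ends at discharge.** For stays beyond 30 days it ends at day 30, and those patients all have equal observation.

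**Conclusion.** The point holds in a limited form. As written, the readmission trigger cannot operate inside the review window on its natural reading, and no stated route brings later admissions to the adjudication committee. Separately, patients with unequal observation are compared as if it were equal. The first conclusion follows from the text alone. The second becomes a bias only if stay differs by condition or calendar period. A 5-day difference in mean stay would then produce about 1 to 3 points, which rests on the assumed stay distribution and constant hazards because the article gives neither. For an exploratory safety outcome this does not threaten the trial's main result, but it is worth correcting because the remedy is nearly free.

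**What to change.** 1. **Analysis.** Replace the chi-squared comparison of ADEs and ADWEs by event rates, with the log of observed days as an offset, in the mixed model with period and cluster. Time to first event, censored at the end of the window, is an alternative and does not need a constant daily rate. Report observed days by condition and period. Admission and discharge dates are enough, so this costs nothing in data collection.
2. **Trigger and window.** Make them agree in one of two ways.
   - Remove the readmission trigger from the in-stay review. This costs nothing.
   - Or define it as an unplanned admission or emergency visit after discharge and up to day 30 from recruitment, and send those events to the adjudication committee. The care-use data are already collected for the 90-day assessment, and the planned time-to-first-use analysis needs their dates. The cost is a few more adjudications, with enough clinical detail on each to judge causality. Count these events separately from in-stay events, or extend their person-time to day 30, so that numerator and offset match.
3. **Wording.** State the reference event for the 48-hour emergency visit trigger as well.

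Extending every Table 2 trigger beyond discharge is not proposed, since it would need laboratory and clinical records from outside the hospital.
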